## 7.6 Pharmacokinetics

(1) Drug concentrations in the liver

[1] Timing of liver biopsy and the acceptable range

Described in the section of “7.4 (1) Liver biopsy.”

[2] Procedure for specimen processing

Collect liver tissue samples for determination of drug concentrations at the same time as liver biopsy prescribed in the section of “7.4 (1) Liver biopsy.” Remove blood from the liver tissue samples collected using a piece of physiological saline-soaked filter paper, with the tissue weight determined using a semi-micro balance. Immerse the tissue samples in a polypropylene container containing 99.5% ethanol and purge the residual space with argon gas. After that, seal and store the container protected from light in a freezer at -80C.

[3] Shipment of the specimens

The study center will send the liver tissue samples for determination of drug concentrations in the frozen state to the facility undertaking determination of drug concentrations.

[4] Procedure of drug concentration determination

To determine the concentrations of unchanged NIK-333 and NIK-333 lipids form in the liver, extract liver samples, obtain derivatives and determine the concentrations by liquid chromatography-atmospheric pressure chemical ionization-tandem mass spectrometry (LC-APCI-MS/MS).

(2) Drug concentration in plasma

[1] Timing of blood sample collection and the acceptable range

- On the day before the start of study drug administration and on the day of evaluation at Week 8 after the start of administration (4 and 8 hours after administration)

- 4 hours after administration: ±30 minutes

- 8 hours after administration: ±30 minutes

- Weeks 24, 48, 72 and 96 after the start of study drug administration

- 4 hours after administration: ±30 minutes

If a deviation from the blood sample collection time is within the acceptable range, the sample will be deemed as being collected at the designated time.

[Rationale for timing of blood sample collection]

On the day before the start of administration and at Week 8 after the start of administration when liver biopsy is performed and the subject is hospitalized for monitoring, collect blood samples at 4 hours after administration, which is close to the time point of the Cmax of unchanged NIK-333, and at 8 hours after administration, which is equivalent to the elimination phase of unchanged NIK-333 and close to the time point of the Cmax of NIK-333 lipids form.

From Week 8 after the start of administration, fixed-point determination will be made only at 4 hours after administration to confirm that NIK-333 and NIK-333 lipids form have reached a steady state during the administration period of 48 weeks or more. Determination of NIK-333 lipids form will provide essential information to be taken into consideration in the cases in which any changes are seen in the blood concentrations of NIK-333, because it is the “strage form” of NIK-333 and present in blood at higher concentrations than NIK-333.

- Follow-up examination of pharmacokinetics

Week 12 after the end of study drug administration

[Rationale for timing of blood sample collection]

To confirm elimination of the study drug from plasma after repeated administration of NIK-333

[2] Procedure of blood sample collection and amount of blood samples

At each time point for blood sample collection, collect 5 mL of blood from the cubital vein into a vacuum blood collection tube using EDTA-2Na as an anticoagulant, immediately mix thoroughly and centrifuge (4C, 3,000 rpm, 15 minutes) to obtain the plasma. Dispense the plasma into 5 tubes of 500 L each. Purge the residual space of 4 of these tubes with argon gas, and seal and store the tubes protected from light in a freezer at -80C. Store the remaining 1 tube for determination of TGF-.

At the time of follow-up examination of pharmacokinetics, collect 2.5 mL of blood, but do not collect any blood samples for the determination of TGF-.

[3] Shipment of the specimens

The study center will send the plasma samples for determination of drug concentrations in the frozen state to the facility undertaking determination of drug concentrations.

[4] Procedure of determination of the concentrations of unchanged NIK-333 and NIK-333 lipids form

To determine the concentrations of unchanged NIK-333 and NIK-333 lipids form in plasma, extract plasma samples, obtain derivatives and determine the concentrations by liquid chromatography-atmospheric pressure chemical ionization-tandem mass spectrometry (LC-APCI-MS/MS).

[5] Determination of metabolites in plasma

The sponsor will determine the concentration of NIK-333-26, a presumed metabolite,in plasma using the plasma samples remaining after determination of unchanged NIK-333 and NIK-333 lipids form in plasma. However, the metabolite can be determined only when the subject’s additional consent has been obtained in advance. The chemical name and structural formula of the presumed metabolite are shown below.

- NIK-333-26

Chemical name: (6*E*,10*E*)-3,7,11,15-tetramethyl-6,10,14-hexadecatrienoic acid

Structural formula:

[6] Procedure of determination of the concentrations of metabolite

To determine the concentration of NIK-333-26, extract the remaining plasma samples, obtain derivatives and determine the concentrations in plasma by liquid chromatography-atmospheric pressure chemical ionization-tandem mass spectrometry (LC-ESI-MS/MS).

(3) Determination of drug concentrations in urine

[1] Timing of urine sample collection

Accumulate urine samples at the time of liver biopsy. In other words, accumulate urine samples for 24 hours from the day before the start of study drug administration (day of liver biopsy), and for 24 hours from immediately after administration at Week 8 of administration.

[2] Procedure of urine sample collection and amount of urine samples

Place each single voided urine sample obtained by natural micturition in a light-protected glass container and store in a refrigerator (4C). Combine single voided urine samples and determine the total urine volume with a glass measuring cylinder. Wash the containers with the same volume of methanol and stir the sample thoroughly. Then, dispense 200 mL each of the sample into 3 designated containers. Purge the residual space of the designated container with argon gas, and store the containers protected from light in a freezer at -80C.

[3] Shipment of the specimens

The study center will send 3 containers of the urine samples in the frozen state to the facility undertaking determination of drug concentrations for determination of drug concentrations. The facility undertaking determination of drug concentrations will keep one of the containers.

[4] Procedures for drug concentration determination

To determine the urinary concentrations of unchanged NIK-333, extract urine samples with diethyl ether/2-propanol, and determine the concentrations by liquid chromatography-ultraviolet spectrophotometry (LC-UV).

[5] Determination of metabolites in urine

The sponsor will determine NIK-333 metabolites in urine when deemed necessary. If a procedure for determining NIK-333 metabolites is established in the future, metabolites can be determined after an additional consent is obtained from the subjects.

## 7.7 Exploratory biomarkers (TGF- concentration in plasma)

In addition to determination of the gene expression profiles in the liver and peripheral blood, determine concentrations of TGF- in plasma to assess its potential as a biomarker associated with gene expression. Moreover, monitor the changes of TGF- concentrations in plasma from Week 8.

[1] Timing of blood collection

- On the day before the start of study drug administration and on the day of evaluation at Week 8 after the start of administration (4 and 8 hours after administration)

- 4 hours after administration: ±30 minutes

- 8 hours after administration: ±30 minutes

- Weeks 12, 24, 36, 48, 60, 72, 84 and 96 after the start of study drug administration

- 4 hours after administration: ±30 minutes

[Rationale for timing of blood sample collection]

In the same way as determination of gene expression profile in peripheral blood, determine TGF- in plasma on the day before the start of administration, at Week 8 after the start of administration (4 and 8 hours after administration), and subsequently at Weeks 12, 24, 36, 48, 60, 72, 84 and 96 after the start of study drug administration to monitor the changes over time and to explore the potential of TGF- as a biomaker.

[2] Procedure of blood sample collection and amount of blood samples

<<Weeks 12, 36, 60 and 84 after the start of administration>>

At each time point for blood sample collection, collect 1 mL of blood from the cubital vein into a vacuum blood collection tube using EDTA-2Na as an anticoagulant, immediately mix thoroughly and centrifuge (4C, 3,000 rpm, 15 minutes) to obtain the plasma. Store the plasma, 500 L, in a freezer at -80C.

<<Day before the start of study drug administration and at Weeks 8, 24, 48, 72 and 96 after the start of administration>>

At each time point for blood sample collection, collect 5 mL of blood from the cubital vein into a vacuum blood collection tube using EDTA-2Na as an anticoagulant, immediately mix thoroughly and centrifuge (4C, 3,000 rpm, 15 minutes) to obtain the plasma. Dispense the plasma into 5 tubes of 500 L each. Store one of them in a freezer at -80C and the remaining 4 tubes as the samples for determination of drug concentrations in plasma.

[3] Shipment of the specimens

The study center will send the plasma samples for TGF- determination in the frozen state to the facility undertaking determination of TGF-.

[4] Procedure of determination

Determine the concentrations of TGF- in plasma by ELISA.

## 7.8 Acceptable range of deviations from the dates of examination, observation and evaluation

The acceptable range of deviation from the scheduled examination, observation and evaluation on the day of the start of administration is the period from completion of radical therapy until the start of study drug administration for bone densitometry, endoscopy, ECG, echocardiography, pulse wave examination and fundus examination and within 14 days before the designated date for other parameters.

The acceptable range of deviation from the scheduled examination, observation and evaluation during the study drug administration period is +28 days for gene expression profile (Week 8), TGF- (Week 8), and liver, plasma and urinary pharmacokinetics (all are at Week 8), ±35 days for abdominal imaging diagnosis, HCV-RNA, HCG tests, tumor markers, fibrosis markers, bone densitometry, endoscopy, ECG, echocardiography, pulse wave examination and fundus examination, and 7 days for other parameters.

The acceptable range of deviation from the scheduled examination, observation and evaluation at follow-up examination (Week 12 after the end of administration) is +28 days.

# 8. Subjects’ treatment compliance and subject management

## 8.1 Subjects’ treatment compliance

The investigator or the subinvestigator will instruct subjects to make sure to bring the remaining study drugs when they visit the outpatient clinic. The investigator or subinvestigator will confirm and record the subjects’ treatment compliance status on the basis of the remaining drugs.

## 8.2 Subject management

The investigator or the subinvestigator will provide guidance to the subjects regarding the following matters.

[1] Health management

1) Instruct the subjects to immediately report any abnormalities observed during the study period to the investigator or the subinvestigator, to visit the hospital as needed, and to receive medical examination and treatment.

2) Premenopausal women will be instructed to make sure to practice contraception during the study period. Conduct the HCG test at 24-week intervals to check for pregnancy.

[HCG tests]

During the study period, test serum HCG (human chorionic gonadotropin) at the time of subject registration and at 24-week intervals during the period from the start of study drug administration until the day of the end of study drug administration. In addition, examine serum HCG at the time of completion/discontinuation of study drug administration if possible. If the study has been discontinued, test serum HCG to the extent possible.

[Rationale]

NIK-333 has been confirmed to be teratogenic and induce miscarriage, and administration to pregnant or potentially pregnant women must be avoided.

[2] Use of other drugs

1) Instruct the subjects to refrain from taking vitamin A products and nutritional supplements of which labeled components include vitamin A (retinol) and vitamin K during the study period.

2) Instruct the subjects to consult with the investigator or the subinvestigator in advance and to follow their directions regarding the intake of other drugs and nutritional supplements during the study period.

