**X Study period**

September 2005 to December 2009

XI Schedule of main examinations, observations and evaluations

| Timing (week)  Parameter | | Registration (within 56 days before) | During study drug administration period | | | | | | | At the time of follow-up examination (Week 12 after completion of study drug administration) | At the time of study discontinuation |
| --- | --- | --- | --- | --- | --- | --- | --- | --- | --- | --- | --- |
| Start of administration (within 14 days before) | Week 4, 28, 52, 76 | Week 8, 32, 56, 80 | Week 12, 36, 60, 84 | Week 16, 40, 64, 88 | Week 20, 44, 68, 92 | Week 24, 48, 72, 96 |
| Study drug administration | |  |  | | | | | | |  |  |
| Examination of compliance status | |  |  | ● | ● | ● | ● | ● | ● |  |  |
| Gene expression profile | |  |  |  |  |  |  |  |  |  |  |
| TGF- | |  |  |  |  | ● |  |  | ● |  |  |
| Drug concentration in the liver | |  |  |  |  |  |  |  |  |  |  |
| Drug concentration in plasma | |  |  |  |  |  |  |  | ● | ● |  |
| Drug concentration in urine | |  |  |  |  |  |  |  |  |  |  |
| Abdominal imaging diagnosis | | ● |  |  |  | ● |  |  | ● | ● |  |
| Medical examination | | ● | ● | ● | ● | ● | ● | ● | ● | ● |  |
| Vital signs, etc. | | ● | ● | ● | ● | ● | ● | ● | ● | ● |  |
| Child-Pugh classification | Encephalopathy / ascites | ● |  |  |  |  |  |  |  |  |  |
| T-Bil,ALB,PT | ● |  |  |  |  |  |  |  |  |  |
| HBs antigen | | ● |  |  |  |  |  |  |  |  |  |
| HCG tests (premenopausal women only) | | ● |  |  |  |  |  |  | ● |  |  |
| Hematology tests  (platelet count, hemoglobin level) | | ● |  |  |  |  |  |  |  |  |  |
| Hematology tests | |  | ● | ● | ● | ● | ● | ● | ● | ● |  |
| Blood biochemistry tests | |  | ● | ● | ● | ● | ● | ● | ● | ● |  |
| Urinary tests (fresh urine) | |  | ● | ● | ● | ● | ● | ● | ● | ● |  |
| Blood pressure parameters | |  | ● |  |  |  |  |  |  |  |  |
| HCV-RNA (quantitative) | | ● |  |  |  |  |  |  |  |  |  |
| HCV-RNA (genotype analysis) | |  | ● |  |  |  |  |  |  |  |  |
| Tumor markers | |  | ● |  |  | ● |  |  | ● | ● |  |
| Fibrosis marker | |  | ● |  |  |  |  |  |  |  |  |
| Bone densitometry (DXA，lumbar vertebrae) | |  | ○ |  |  |  |  |  |  |  |  |
| Endoscopy | |  | ○ |  |  |  |  |  |  |  |  |
| ECG | |  | ○ |  |  |  |  |  | ● |  |  |

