## 4.8 Amount of blood collected and the number of days of blood collection

The amount of blood collected from the subject on each visit is shown below.

As the laboratory test facility switches to a different method of HCV-RNA test (quantitative), the amount of blood collected will increase from 34 mL to 39 mL beginning in August 2008 for the days of evaluation on Week 48 and Week 96 of study drug administration.

|  | Amount of blood collected per day (ml) | Number of days of blood collection |
| --- | --- | --- |
| At the time of registration | 12 | 1 |
| Day of the start of administration | 39 | 1 |
| Day of evaluation at Week 8 of administration | 39 | 1 |
| Days of evaluation at Weeks 12, 36, 60 and 84 of administration | 18 | 4 |
| Days of evaluation at Weeks 24 and 72 of administration | 24 | 2 |
| Days of evaluation at Weeks 48 and 96 of administration | 39 | 2 |
| Days of evaluation at Weeks 4, 16, 20, 28, 32, 40, 44, 52, 56, 64, 68, 76, 80, 88 and 92 of administration | 14 | 15 |
| At the time of follow-up examination (Week 12 after completion of administration) | 22 | 1 |
| Total | 520 | 27 |

This table does not include any blood samples collected at the discretion of the investigator or the subinvestigator due to the occurrence of adverse events, etc.

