Conduct examination/observation/investigation upon subject registration and during the study drug administration period according to the following schedule.

| Timing (week)  Parameter | | Registration (within 56 days before) | During study drug administration period | | | | | | | At the time of follow-up examination (Week 12 after completion of study drug administration) | At the time of study discontinuation |
| --- | --- | --- | --- | --- | --- | --- | --- | --- | --- | --- | --- |
| Start of administration  (within 14 days before) | Weeks 4, 28, 52, 76 | Weeks 8, 32, 56, 80 | Weeks 12, 36, 60, 84 | Weeks 16, 40, 64, 88 | Weeks 20, 44, 68, 92 | Weeks 24, 48, 72, 96 |
| Study drug administration | |  |  | | | | | | |  |  |
| Examination of compliance status | |  |  | ● | ● | ● | ● | ● | ● |  |  |
| Gene expression profile | |  |  |  |  |  |  |  |  |  |  |
| TGF- | |  |  |  |  | ● |  |  | ● |  |  |
| Liver drug concentration | |  |  |  |  |  |  |  |  |  |  |
| Plasma drug concentration | |  |  |  |  |  |  |  | ● | ● |  |
| Urinary drug concentration | |  |  |  |  |  |  |  |  |  |  |
| Abdominal imaging diagnosis | | ● |  |  |  | ● |  |  | ● | ● |  |
| Medical examination | | ● | ● | ● | ● | ● | ● | ● | ● | ● |  |
| Vital signs, etc. | | ● | ● | ● | ● | ● | ● | ● | ● | ● |  |
| Child-Pugh classification | Encephalopathy/ascites | ● |  |  |  |  |  |  |  |  |  |
| T-Bil, ALB, PT | ● |  |  |  |  |  |  |  |  |  |
| HBs antigen | | ● |  |  |  |  |  |  |  |  |  |
| HCG tests (premenopausal women only) | | ● |  |  |  |  |  |  | ● |  |  |
| Hematology tests  (platelet count, hemoglobin level) | | ● |  |  |  |  |  |  |  |  |  |
| Hematology tests | |  | ● | ● | ● | ● | ● | ● | ● | ● |  |
| Blood biochemistry tests | |  | ● | ● | ● | ● | ● | ● | ● | ● |  |
| Urinary tests (fresh urine) | |  | ● | ● | ● | ● | ● | ● | ● | ● |  |
| Blood pressure parameters | |  | ● |  |  |  |  |  |  |  |  |
| HCV-RNA (quantitative) | | ● |  |  |  |  |  |  |  |  |  |
| HCV-RNA (genotype analysis) | |  | ● |  |  |  |  |  |  |  |  |
| Tumor markers | |  | ● |  |  | ● |  |  | ● | ● |  |
| Fibrosis marker | |  | ● |  |  |  |  |  |  |  |  |
| Bone densitometry (DXA，lumbar vertebrae) | |  |  |  |  |  |  |  |  |  |  |
| Endoscopy | |  |  |  |  |  |  |  |  |  |  |
| ECG | |  |  |  |  |  |  |  | ● |  |  |

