## 7.5 Safety

(1) Indicators for safety evaluation

[1] Examinations for confirming recurrence

The investigator or the subinvestigator will perform imaging diagnosis by abdominal ultrasonography (US) and dynamic CT or dynamic MRI at 12-week intervals during the study drug administration period, as well as at the time of follow-up examination. If recurrence is suspected based on any other findings (such as gradual increase of tumor markers), imaging diagnosis by dynamic CT or dynamic MRI will be performed as needed.

[2] Other examinations for confirming recurrence

The investigator will precisely look for the recurrence of HCC by determining the levels of tumor markers during the study drug administration period. If recurrence is suspected by this determination, perform imaging diagnosis by dynamic CT or dynamic MRI as needed.

Tumor markers tests:

Determine AFP, AFP-L3 and PIVKA-II at 12-week intervals from the day of the start of study drug administration (within 14 days before the start) until the last day of study drug administration, and as well as at the time of follow-up examination.

If the study has been discontinued, AFP, AFP-L3 and PIVKA-II will be tested to the extent possible.

[3] Examinations related to the underlying disease

The investigator will perform HCV-RNA tests and fibrosis markers tests so as to examine the underlying disease during the study drug administration period.

1) HCV-RNA tests (quantitative)

Perform HCV-RNA tests at the time of registration (within 56 days before administration) and at 48-week intervals from the start of study drug administration until the end of study drug administration. Conduct genotype analysis on the day of the start of administration.

If the study is discontinued, perform HCV-RNA test to the extent possible.

2) Fibrosis markers tests

Perform hyaluronic acid test at 48-week intervals from the start of study drug administration (within 14 days before the start of administration) until the end of study drug administration.

If the study has been discontinued, hyaluronic acid will be tested to the extent possible.

[4] Medical examination

Examine symptoms and signs at 4-week intervals from the start of study drug administration (within 14 days before the start of administration) until the end of study drug administration, and at the time of follow-up examination.

If the study has been discontinued, symptoms and signs will be examined to the extent possible.

[5] Vital signs, etc.

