| Endoscopy | Esophagus, stomach |
| ECG | 12-lead |
| Echocardiography | M mode echocardiogram, two-dimensional echocardiogram, Doppler echocardiogram, etc. |
| Pulse wave examination | Pulse wave velocity (PWV)/ankle brachial index (ABI) |
| Fundus examination | Fundus photographs |

*: Menopausal status and whether or not being pregnant will be confirmed for female subjects.

#:Conducted only on the day of the start of administration

Table 3 Examination, observation and evaluation parameters at the time of follow-up examination

| Examination parameters | Examination, observation and evaluation parameters |
| --- | --- |
| Pharmacokinetics | Drug concentration in plasma (unchanged NIK-333 and NIK-333 lipids form) |
| Abdominal imaging/  diagnosis | Presence or absence of HCC on dynamic CT, US, and MRI images |
| Medical examination | Symptoms*, signs |
| Vital signs, etc. | Body temperature (axillary), blood pressure (systolic/diastolic: dorsal position or sitting position), pulse rate (dorsal position or sitting position), body height#, body weight |
| Hematology tests | White blood cell count, red blood cell count, hemoglobin level, hematocrit, platelet count |
| Blood biochemistry tests | Total protein, albumin, bilirubin, total cholesterol, LDL cholesterol, HDL cholesterol, triglyceride, blood glucose, urea nitrogen, Cl, Na, K, Ca, ALP, AST, ALT, LDH, -GTP, choline esterase, serum creatinine, A/G ratio, free fatty acid, 2-microglobulin |
| Tumor markers | AFP，AFP-L3，PIVKA-II |
| Urinary tests (fresh urine) | Qualitative (glucose, protein, urobilinogen, ketone body, occult blood)  urinary albumin (converted to creatinine), urinary sediments (red blood  cells, white blood cells, epithelial cells, columnar cells, others)  2-microglobulin |

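### No HCG assay is scheduled at the start of dosing: the pre-dose result may be up to 56 days old and the next assay is at Week 24

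*Protocol*

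**What the plan says.** Section 8.2 of the Protocol tells sites, for premenopausal women, to "test serum HCG (human chorionic gonadotropin) at the time of subject registration and at 24-week intervals" over the dosing period, with a further test at completion or discontinuation if possible. Its rationale is that NIK-333 is teratogenic and causes miscarriage, so "administration to pregnant or potentially pregnant women must be avoided". Section 2.3 gives the animal findings: teratogenicity in rats from 100 mg/kg/day and in rabbits at 270 mg/kg/day, with miscarriage in rabbits at that dose.

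The visit grid appears twice, in the Summary of Study Plan (XI) and in section 7.3. In both, the row "HCG tests (premenopausal women only") is marked at registration and in the Week 24, 48, 72 and 96 column only. The column headed "Start of administration (within 14 days before") is blank for HCG, while hematology, biochemistry, urine tests and tumor markers are marked there.

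Other safeguards exist:

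- Exclusion criterion [11] bars women who are or may be pregnant.
- Section 8.2 requires instruction on contraception.
- Section 10.1 (1) [6] stops treatment if pregnancy is found.
- The medical examination carries a footnote in Table 2: "Menopausal status and whether or not being pregnant will be confirmed for female subjects". Section 7.5 times that examination as follows: "Examine symptoms and signs at 4-week intervals from the start of study drug administration (within 14 days before the start of administration").

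**The concern.** The protocol repeats routine laboratory tests within 14 days before dosing, but not the one assay aimed at the hazard it treats as a bar to dosing. An eligibility HCG can be negative at registration and be overtaken by a conception before the first dose. An early pregnancy that is not apparent at a medical examination would then be exposed to the drug. The discontinuation rule acts only once pregnancy has been found, which is after exposure. The stake is the safety of the subject and the fetus; the statistical results are not touched.

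**Working it through.** No power or sample-size figure is involved. The check is a reading of the schedule plus day counts.

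**1. Age of the pre-dose assay.** The registration column in both grids says within 56 days before, without naming the anchor. Two sections supply one:

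- Section 7.5, for the registration HCV-RNA sample: "Perform HCV-RNA tests at the time of registration (within 56 days before administration"). Applied to HCG, the longest gap from assay to first dose is 56 days.
- Section 7.1, which does list HCG among the eligibility tests, counts 56 days back from registration. The gap is then at most 56 + d days, where d is the time from registration to first dose. Inclusion criterion [4] limits CT-to-dose time to 56 days but sets no such limit for HCG.

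The first reading gives the smaller figure, so 56 days is used below.

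**2. First on-treatment assay.** Week 24 is 24 × 7 = day 168. Section 7.8 allows ±35 days for HCG: 168 − 35 = 133 and 168 + 35 = 203, so the range is day 133 to day 203. Five visits with a medical examination and a blood draw (Weeks 4, 8, 12, 16 and 20) precede the nominal Week 24 visit without an assay.

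**3. Longest time between the two assays.** 56 + 168 = 224 days nominally; 56 + 168 + 35 = 259 days with the latest permitted Week 24 test.

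**4. Does the 24-week wording in 8.2 include Week 0?** The sentence goes on to count the intervals over the period from the start to the end of dosing, so the wording alone leaves the question open. Comparison with other tests settles it:

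| Test | Text | Start cell in the grids |
| --- | --- | --- |
| Medical examination, vital signs, laboratory tests, tumor and fibrosis markers | intervals from the start, with an explicit 14-day pre-dose window | marked |
| Blood pressure parameters | 48-week intervals from the start; Note 3 names the day of the start | marked |
| HCV-RNA (quantitative) | registration, then intervals from the start | blank |
| HCG | registration, then intervals from the start | blank |

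HCG follows the HCV-RNA pattern. Where a start-day test is intended, the text or a note says so and the grid marks it.

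**5. Effect of a start-visit assay.** With the general 14-day window, the longest gap from assay to first dose falls from 56 to 14 days: 56 − 14 = 42 days shorter.

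**The case against.** The strongest reply is that pregnancy is already checked close to dosing. The Table 2 footnote requires pregnancy status to be confirmed at an examination due within 14 days before the start, exclusion [11] bars even possible pregnancy, and contraception is instructed. On this view 8.2 is put into practice and only the method of confirmation is unnamed. That much is right: the gap is in the assay, not in all pregnancy checking. It does not close the gap, because a confirmation with no stated method can miss a pregnancy that is not yet apparent.

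A second reply is that Table 2 covers the day of the start of administration and lists HCG. However, Note 4 to the schedule refers to Table 2 for the contents of the tests; visit timing is set by the grids and 8.2. If a start-day assay was intended, both grids are wrong and need the same correction.

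Third, the 56 days comes from the HCV-RNA paragraph and is not a stated HCG limit. That is correct. It is an inferred maximum, not an expected delay, and the alternative anchor in 7.1 can only lengthen it.

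Fourth, calendar days are not risk. The protocol does not give the number of premenopausal women, and a result up to 14 days old has a blind period of its own. Both points stand. They limit the weight of the finding but do not remove it.

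Finally, the wait until Week 24 is not shortened by a start-visit assay. That is also true; those figures describe the schedule and are not the target of the fix.

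**Conclusion.** The concern holds. A site that follows the protocol to the letter can start a premenopausal woman on NIK-333 on an HCG result up to 56 days old, with no further scheduled assay until Week 24 (day 133 to 203). The 56 days assumes that the registration window is counted back from administration, as 7.5 states for HCV-RNA; it could be longer under 7.1.

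The practical reach is probably small: 12 subjects, of whom an unstated number are premenopausal, with several non-assay safeguards in place. No endpoint, analysis set or estimate is affected. The change is still worth making, because the possible harm is severe and irreversible and the correction is cheap.

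**What to change.** Add serum HCG, premenopausal women only, to the start-of-administration column in both grids (Summary XI and section 7.3) and to the HCG paragraph of 8.2. Require a negative result before the first dose.

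The sample should come from blood already taken for the start visit, early enough for the result to be back in time. Section 4.8 plans 39 mL for the day of the start of administration. Note 2 to the schedule has subjects bled on the biopsy day, with dosing 24 hours after the procedure. A sample drawn only on the morning of dosing might not be reported in time, so the amendment should name the draw.

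The cost is one assay per premenopausal woman, a turnaround constraint before the first dose, and a short amendment.

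Moving HCG from the ±35-day to the 7-day group in 7.8 and in Note 1 of both grids is optional. It would place the first on-treatment assay at day 161 to 175 (168 ± 7) without changing the 24-week interval, and it is not needed to close the pre-dose gap.
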